### Study endpoints

Primary outcome measures are the absolute and percent change in CHD from baseline with CD compared with AD. CHD is defined as the total heparin received per dialysis session. Secondary outcomes are the effect of CD compared with AD on systemic anticoagulation (prothrombin time [PT]/international normalised ratio [INR], activated partial thromboplastin time [aPTT]), intradialytic metabolic parameters (serum total serum calcium, ionized calcium, magnesium, bicarbonate), anaemia, haemodynamic stability (blood pressure, heart rate, corrected QT interval, number of HD sessions complicated by intradialytic hypotension), dialysis adequacy (single pool Kt/V, urea reduction ratio, beta-2-microglobulin [B2M]), systematic inflammation (C-reactive protein [CRP]), bleeding time after HD, and bleeding events. Also, the visual clotting score and the dialyser fibre bundle volume (FBV) (as measured by the ultrasound dilution technique [35]) are correlated. Lastly, the intra-rater and inter-rater reliability of the visual clotting score is assessed.

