**Methods:**

This double-blinded, randomised, cross-over trial of chronic haemodialysis patients determines if CD allows reduction in CHD during HD compared with AD. After enrolment, intradialytic heparin is minimised during a two-week run-in period using a standardised protocol based on a visual clotting score. Patients still requiring intradialytic heparin after the run-in period are randomised to two weeks of HD with AD followed by two weeks of CD (Sequence 1) or two weeks of HD with CD followed by two weeks of AD (Sequence 2). The primary outcome is the change in CHD with CD compared with AD. Secondary outcomes include metabolic and haemodynamic parameters, and dialysis adequacy.

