### Study protocol

After enrolment, each patient’s dose of intradialytic heparin is minimised during a two-week run-in period (Fig. 1) using study protocol (Table 1) which is based on a standardised visual clotting score [34]. The visual clotting score is quantified by inspecting the venous chamber and all four quadrants of the dialyser at the end of the HD session (0: clear dialyser/no clots; 1: few strands/small clots; 2: half clotted; 3: three-quarters clotted; 4: completely clotted, unable to return blood) (Table 1). The heparin dose is reduced to reach a target visual clotting score of 2, then increased slightly and maintained, to achieve the lowest possible dose required to prevent clotting (Table 1). The CHD during the last HD session of the run-in period is considered to be the patient’s baseline heparin dose. Patients still requiring intradialytic heparin after the two-week run-in period, and who still meet inclusion and exclusion criteria, are randomised to one of two treatment sequences (Fig. 1). For sequence 1, patients undergo six HD sessions over two weeks with AD (control), followed by six HD sessions over two weeks with CD (intervention). For sequence 2, patients undergo six HD sessions over two weeks with CD (intervention), followed by two weeks of AD (control) (Fig. 1). Patients begin each study phase (AD and CD) with their baseline intradialytic heparin dose, determined at the end of the run-in period. Nurses subsequently adjust intradialytic heparin dose per protocol (Table 1) during each HD session of each study phase. At the end of the first study phase (two weeks), a 68-h washout period ensures no potential for a carry-over effect. After the wash-out period, patients cross-over to the other treatment for the next two weeks beginning again with their baseline heparin dose (Fig. 1). A two-week duration for each strategy is chosen to ensure adequate time to attain the minimum required heparin dose.

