### Cumulative heparin dose

The CHD is calculated per HD session, and determined from HD run sheets. Specifically, CHD is the initial heparin bolus, plus the hourly heparin infusion rate multiplied by the time on HD during which heparin is infused, per session, in heparin units. For the primary outcome, the CHD for the last two HD runs of each study phase are recorded, averaged, and used to calculate change from baseline CHD. The last two HD sessions of each phase is chosen to allow adequate time in each phase for heparin dose minimisation.

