## Statistical analysis

Baseline characteristics will be presented as means and 95 % confidence intervals (CIs) or medians and interquartile range (IQR) for continuous variables, and absolute and relative proportions for categorical variables. To determine the effect of CD compared with AD on reduction in CHD (the primary outcome) a random intercept linear mixed model will be used, with CD or AD as the main exposure, subjects as source of random effects, baseline heparin dose values as covariate (at least 2 of 3 measures from the first of two weeks of each period), and final heparin dose values as outcome (at least 2 of 3 measures of the second week of each period). This model takes into account the correlation of data caused by repeated measures for each subject given the crossover design of the study. Treatment, treatment period, and treatment sequence will be modelled as fixed effects. If there is no evidence of period or carry-over effects, all comparisons will be presented relative to AD, without the need for consideration of carry-over effects.

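### Absolute and percent change in heparin dose are both named primary with no deciding rule; only the unit scale has an analysis, and that model does not match the endpoint as defined

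*Protocol article*

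**What the plan says.** All references are to the protocol article.

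- **Abstract, Methods:** one primary outcome with no scale given: "The primary outcome is the change in CHD with CD compared with AD".
- **Study endpoints:** two measures: "Primary outcome measures are the absolute and percent change in CHD from baseline with CD compared with AD". No order, no requirement that both be met and no split of alpha is given.
- **Study protocol:** the baseline is one session: "The CHD during the last HD session of the run-in period is considered to be the patient’s baseline heparin dose".
- **Cumulative heparin dose:** the endpoint is built from the end of each phase: "the CHD for the last two HD runs of each study phase are recorded, averaged, and used to calculate change from baseline CHD".
- **Sample size calculations:** mean dose 3000 units, SD 900 units, target reduction 1000 units (also labelled 30%), alpha 0.05, power 80%, 30% dropout, 20 patients.
- **Statistical analysis:** one random intercept mixed model is tied to the primary outcome. Its covariate is "baseline heparin dose values as covariate (at least 2 of 3 measures from the first of two weeks of each period" and its outcome is "final heparin dose values as outcome (at least 2 of 3 measures of the second week of each period". Percent change is not mentioned.

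**The concern.** There are two linked problems.

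**No deciding scale.** Absolute and percent change are computed from the same doses but weight patients differently. For the absolute measure the shared run-in baseline cancels. For the percent measure it is the divisor, and it comes from a single session after heparin has been deliberately minimised. Patients with a small baseline therefore count for more on the percent scale. If the two scales disagree, the article gives no way to say whether the primary outcome was met.

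**Endpoint and model do not match.** The endpoint is a change from the last run-in session. The model adjusts instead for doses recorded after the phase has begun. Each phase starts at the run-in dose and is then adjusted after every session by clotting score, so first-week doses can already carry part of the dialysate effect. Conditioning on them can remove part of the effect the trial is meant to estimate.

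**Working it through.** **1. The plan's own figure.** Inputs from Sample size calculations: SD 900, difference 1000, alpha 0.05 (taken as two-sided), power 80%, dropout 30%. The within-patient correlation is not given; 0 is assumed.

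SD of the paired difference = 900 × √2 = 1273.

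n = (1.960 + 0.842)² × 1273² / 1000² = 7.85 × 1.62 = 12.7, so 13 completers. 13 / 0.70 = 18.6, so 19, against the stated 20. A t-based version gives 15 completers, and 15 / 0.70 = 21.4, so 22. The stated 20 is reproduced closely enough, and it is a calculation in units. The percent label is loose: 1000 / 3000 = 33.3%, and 30% of 3000 is 900. Expected completers are 20 × 0.70 = 14.

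**2. What each scale measures within a patient.** Let B be the run-in baseline, C the citrate-phase mean and A the acetate-phase mean.

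- Absolute: (C − B) − (A − B) = C − A. B drops out.
- Percent: 100 × (C − A) / B. B stays as the divisor.

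A 500-unit difference is 500 / 3000 = 17% at a baseline of 3000 units and 500 / 500 = 100% at a baseline of 500, a 6-fold ratio. The Table 1 footnote sets 500 units as the lowest boost and 500 units/h as the lowest running dose, each discontinued below that level. A baseline of 500 is thus reachable, but essentially only on boost alone. With the minimum infusion over an assumed 3 to 4 hours the dose is at least 1500 to 2000 units, and the ratio falls to 3000 / 2000 = 1.5 up to 3000 / 1500 = 2.

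**3. Type I error if either scale could win.** Two paired t-tests at 0.05 on the same simulated patients, no treatment effect, log-normal baselines, 100,000 trials per setting. The ranges cover constant scatter and scatter proportional to baseline.

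| Baseline CV | 14 patients | 20 patients |
|---|---|---|
| 0.3 (900 / 3000, documented) | 5.8–5.9% | 5.8–5.9% |
| 0.6 (assumed) | 6.1–6.3% | 6.4% |

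Independent tests would give 1 − 0.95² = 9.75%. The two scales are strongly correlated, so the real figure is much lower.

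**4. How often the scales disagree.** 14 completers, a mean reduction of 1000 units (constant or proportional to baseline), SD of the difference 1273, baselines floored at 500 units. Exactly one of the two tests was significant in about 7 to 9% of trials at CV 0.3 and about 15 to 22% at CV 0.6.

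**5. The model against the endpoint.**

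| Element | Endpoint sections | Statistical analysis section |
|---|---|---|
| Baseline | last run-in session, one value per patient | first-week doses of each period, on treatment |
| Final value | mean of sessions 5 and 6 of six | at least two of sessions 4, 5 and 6 |
| Scale | absolute and percent change | final dose in units |

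One simulated crossover data set of 14 patients shows what the covariate can do. It was built with citrate lowering first-week dose by 400 units and a total effect of 0.8 × 400 + 500 = 820 units.

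- Final dose, run-in baseline as covariate: −734.4 (SE 135.8).
- Change from run-in baseline, same covariate: −734.4 (SE 135.8), identical.
- Final dose, first-week dose as covariate: −385.2 (SE 111.4).

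The gap depends on the assumed early effect and is an illustration, not a forecast.

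**The case against.** The strongest reply is that the article describes one quantity, tested in units and also expressed as a percentage. One model is tied to the primary outcome, the trial is sized in units, and the abstract speaks of a single outcome. A condensed article may leave the ranking of two expressions to an analysis plan that is not shown. Percent change is also a reasonable scale if savings are proportional to dose.

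Much of this stands. Three stronger readings are tempting, and the document does not support them:

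- *The trial may claim success on whichever scale is significant.* No second test is described, so this is an inference. Even if it were allowed, the excess error at the documented CV is only about 0.9 percentage points.
- *The model analyses neither primary measure.* A final-dose model with the run-in baseline as covariate, or with none, does analyse absolute change, as step 5 shows. Only percent change has no analysis. The fault on the absolute side is the choice of covariate and outcome window.
- *Low-dose patients dominate the percent result.* The 6-fold weight applies to a boost-only patient, and nothing says how many there would be. Such a patient also cannot save more than 500 units.

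The reply does not remove the fact that the article itself labels both scales primary without saying which decides. Nor does it answer the mismatch of baseline and window, which is a contradiction within the article and not a detail deferred to another document.

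**Conclusion.** The point holds in a limited form. Two measures carry primary status, no rule decides between them, and percent change has neither an analysis nor a sample-size basis. The effect on type I error is small: about 5.9% against 5% at CV 0.3, and 6.1 to 6.4% at an assumed CV of 0.6, and only if either scale were allowed to claim success. An unresolved primary result matters more, at about 7 to 9% of trials at CV 0.3 and 15 to 22% at CV 0.6 under the planned 1000-unit effect.

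Separately, the model's baseline and outcome window contradict the endpoint definition, and the first-week covariate can absorb part of the citrate effect by an amount the article does not allow one to fix.

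These figures assume two-sided tests, zero within-patient correlation and log-normal baselines. The CV of 0.3 describes the local dose distribution, not the dose after run-in minimisation, for which no spread is given. This should be corrected, but it does not invalidate the design.

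**What to change.** 1. In Study endpoints, name one primary outcome: the within-patient citrate-minus-acetate difference in mean cumulative heparin dose, in units, over the last two sessions of each phase. Use the same wording in the abstract.
2. Report percent reduction as supportive. One option is the model-based difference divided by the acetate mean, which avoids averaging individual percentages over small baselines.
3. In Statistical analysis, use the last run-in session as the baseline covariate, or no baseline covariate, and the mean of the last two sessions of each phase as the outcome. Drop the first-week doses as covariate.

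The cost is wording only. The sample size does not change, because it is already calculated in units, and the sole loss is the primary status of percent change.

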## Data collection

### Baseline characteristics

Baseline patient demographics (age, gender, HD vintage, race), comorbidities, cause of ESRD, labs, and HD prescription (dialyser, dialysate composition and temperature, blood and dialysate flow rates, target weight, anticoagulation) are extracted from HD charts and the Southern Alberta Renal Program database [36].

### Cumulative heparin dose

The CHD is calculated per HD session, and determined from HD run sheets. Specifically, CHD is the initial heparin bolus, plus the hourly heparin infusion rate multiplied by the time on HD during which heparin is infused, per session, in heparin units. For the primary outcome, the CHD for the last two HD runs of each study phase are recorded, averaged, and used to calculate change from baseline CHD. The last two HD sessions of each phase is chosen to allow adequate time in each phase for heparin dose minimisation.

### Visual clotting score, inter-and intra-rater reliability

The clotting score is a visual grade of dialyser and venous chamber clotting (Table 1). To ensure consistency, scoring of dialyser/venous chamber clotting for heparin dose adjustments are performed at the end of each HD session by a single, trained research nurse. A second HD nurse independently and blindly scores the dialyser/venous chamber appearance; this second clotting score is recorded to assess inter-rater reliability, but is not used to adjust the heparin dose per protocol. To assess for intra-rater reliability, at the end of each HD session during the run-in phase, the dialyser quadrants are captured in four photographs by the same trained research nurse, using a digital camera on a tripod, with standardised lighting, at a standardised distance and height from the dialyser. The dialyser is rotated by 90° for each of the four photographs, to visually capture the full circumferential view of the dialyser. The photographs are re-presented in a blinded fashion to the same research nurse at a later date to be re-scored.

### Metabolic, anticoagulation, and inflammatory parameters

Serum total calcium, ionized calcium, albumin, magnesium, bicarbonate, haemoglobin, urea, PT/INR, aPTT, B2M, and CRP are collected at the beginning of the first HD session of the study (whether randomised to Sequence 1 or 2), and drawn again both pre and post HD for the last HD sessions of each study phase. Ionized calcium is drawn pre and post HD during the first and last HD session in each study phase.

### Haemodynamic parameters

Blood pressure and heart rate are measured and recorded by HD nurses pre and post HD, and every 30 min during HD. The number of HD sessions complicated by intradialytic hypotension (IDH) during each study phase is recorded. IDH is defined as a drop in the systolic blood pressure (SBP) by ≥ 20 mmHg to < 100 mmHg with patient symptoms or nursing/physician intervention. If the patient’s pre-HD SBP is < 100 mmHg, then IDH is defined as a drop in SBP ≥ 10 mmHg with patient symptoms or nursing/physician intervention. An electrocardiogram is performed at baseline (after the run-in phase), as well as pre and post HD during the last HD session in each two week study phase.

### Dialysis adequacy

Single pool Kt/V is determined for each HD session using Diascan® (Hospal-Gambro, Mirandola, Italy), which measures the dialysance of sodium through the dialyser membrane corrected for recirculation and ultrafiltration [37], and which is a validated method for measuring urea clearance [38]. In addition, the urea reduction ratio is calculated for the last HD session of each study phase using the equation ((urea pre—urea post)/urea pre).

### Bleeding time and bleeding events

For the last two HD sessions of each study phase, the bleeding time post-HD is recorded and averaged in patients who have a fistula or graft as their vascular access. Bleeding events are documented and classified into: 1) major bleeding (fatal bleeding, overt bleeding associated with a haemoglobin drop ≥ 20 g/L and/or transfusion with 2 units of red blood cells, retroperitoneal/intracranial/intraspinal/intra-ocular/pericardial/non-traumatic intra-articular bleeding), 2) clinically important non-major bleeding (clinically overt bleeding requiring hospital admission or visit to a medical facility or leading to intervention), and 3) minor bleeding (any bleeding episode not meeting criteria for the preceding bleeding categories).

### Fibre bundle volume

FBV is the space within the blood compartment of hollow fibre dialysers [35]. Using the ultrasound dilution technique (Transonic® HD02 monitor, Transonic Systems Inc.®, Ithaca, NY, USA), dialyser FBV is measured twice (and the mean recorded) during both the first and last 30 min of the mid-week HD sessions throughout the entire study period (including the run-in phase). The change in FBV during HD represents the quantity of clot in the dialyser [35] and is determined using the equation ((FBV pre—FBV post)/FBV pre).

## Sample size calculations

Previous studies have demonstrated that CHD is reduced by 30 % with the use of CD [39]. Locally in Calgary, the mean CHD is 3000 units (standard deviation 900 units) per HD session in 85 % of HD patients. Based on this, and taking into account a 30 % dropout rate, we estimate that 20 patients are required to demonstrate a 30 % (1000 units) reduction in CHD with CD compared to AD (alpha 0.05, power 80 %). We use the method of Frison and Pocock for the ANCOVA model, and Rabe-Hesketh and Skrondal for the mixed linear model solution (StataCorp LP version SE 11.0, College Station, TX, USA).

## Statistical analysis

Baseline characteristics will be presented as means and 95 % confidence intervals (CIs) or medians and interquartile range (IQR) for continuous variables, and absolute and relative proportions for categorical variables. To determine the effect of CD compared with AD on reduction in CHD (the primary outcome) a random intercept linear mixed model will be used, with CD or AD as the main exposure, subjects as source of random effects, baseline heparin dose values as covariate (at least 2 of 3 measures from the first of two weeks of each period), and final heparin dose values as outcome (at least 2 of 3 measures of the second week of each period). This model takes into account the correlation of data caused by repeated measures for each subject given the crossover design of the study. Treatment, treatment period, and treatment sequence will be modelled as fixed effects. If there is no evidence of period or carry-over effects, all comparisons will be presented relative to AD, without the need for consideration of carry-over effects.

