**Fig. 1 Fig1:**
[figure not shown]
Study Flow Diagram

**Table 1 Tab1:** Visual Clotting Score and Heparin Protocol

Clotting Score	Dialyser/Venous Chamber Appearance (at the end of each HD session)	Heparin Dose Adjustment (for the next HD session)
0	Clear	Decrease^a^ boost by 200 units *and* decrease running dose by 200 units/h
1	Few strands/small clot	Decrease^a^ boost by 200 units *and* decrease running dose by 200 units/h
2	½ clotted	Increase boost by 200 units *and* increase running dose by 200 units/h and *maintain* this new heparin dose for the remainder of this study phase only.
3	¾ clotted (able to return blood)	Increase boost by 300 units *and* increase running dose by 300 units/h
4	Completely clotted (unable to return blood)	Increase boost by 400 units *and* increase running dose by 400 units/h

*HD* haemodialysis

NOTE

1) If there is unusually prolonged bleeding from vascular access sites post-HD, for the next HD session, decrease^a^ heparin running dose by 200 units/h and turn heparin off 30 min earlier than usual

2) If there is a discrepancy in score between the dialyser and the venous chamber, the heparin dose adjustment is based on the dialyser clotting score

^a^The minimum possible heparin boost and running dose are 500 units (boost) and 500 units/h. If the heparin dose is to be decreased to less than 500 units (boost and/or running dose) for the next HD session, discontinue the boost and/or the running dose

Randomisation is determined by a computer generated random number list and concealed in sequentially numbered, opaque, sealed envelopes to ensure allocation concealment. Following informed consent and enrolment, the envelope containing allocation sequence is provided to the research coordinator who implements the sequence assignment according to protocol. The intervention and control dialysates, CD and AD, are packaged identically by the manufacturer (Chief Medical Supplies, Ltd., Calgary, Alberta, Canada) for blinding of investigators, patients, and health care staff. All data is confidential, and entered into electronic records by an independent data entry clerk who is blinded to patient allocation.

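### The primary model adjusts for a baseline heparin dose measured on treatment in week 1 of each period, which removes part of the citrate effect it is meant to estimate

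*Protocol article*

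**What the plan says.** The article describes baseline dose in two ways.

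- **Study protocol section.** "The CHD during the last HD session of the run-in period is considered to be the patient’s baseline heparin dose". This is one pre-randomisation value per patient, shared by both phases. The Study endpoints and Cumulative heparin dose sections express the primary outcome as change from baseline CHD, the latter using the average of the last two sessions of each phase.
- **Statistical analysis section.** The random-intercept model has treatment, period and sequence as fixed effects. Its covariate is "baseline heparin dose values as covariate (at least 2 of 3 measures from the first of two weeks of each period", and its response is "final heparin dose values as outcome (at least 2 of 3 measures of the second week of each period".

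Two further statements settle when the week-1 doses become treatment-dependent: "Patients begin each study phase (AD and CD) with their baseline intradialytic heparin dose, determined at the end of the run-in period", and "Nurses subsequently adjust intradialytic heparin dose per protocol (Table 1) during each HD session of each study phase". Table 1 sets the next session's dose from the clotting score at the end of the current one. For a clear or nearly clear dialyser the downward step is "boost by 200 units *and* decrease running dose by 200 units/h".

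**The concern.** A covariate in the primary model should not be something the treatment can change. Session 1 of a phase is given at the run-in dose. The doses at sessions 2 and 3 respond to clotting seen under that phase's dialysate. The week-1 mean therefore lies on the path from dialysate to week-2 dose, and conditioning on it leaves only the part of the CD effect not already expressed in week 1.

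Period-specific baselines can be legitimate in a crossover if they are taken before that period's treatment. Here the pre-treatment dose is by design the same run-in value in both phases, so the week-1 doses add no pre-treatment information about the period.

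At stake is the primary estimate itself: in a trial of 20 patients, a real heparin saving could be reported as small or non-significant.

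**Working it through.** **1. The plan's own sample size, for scale.** The Sample size calculations section gives SD 900, difference 1000 units, alpha 0.05, power 80%, 30% dropout and 20 patients. With the paired formula n = 2(1−ρ)[SD(z₀.₉₇₅+z₀.₈₀)/δ]² and ρ = 0 (the article states no correlation), n = 2 × (900 × 2.80/1000)² ≈ 12.7, so 13. Allowing for dropout, 13/0.7 = 18.6, so 19. Fourteen completers give 14/0.7 = 20 exactly. The stated figure is reproduced to within one patient and is not in question here.

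**2. What the adjusted coefficient estimates.** Let Δ₁ and Δ₂ be the CD−AD differences in mean dose in weeks 1 and 2, and b the covariate slope. Then

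adjusted effect = Δ₂ − b × Δ₁.

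With the run-in dose as covariate, the two phases of a patient share one value, so Δ₁ = 0 and the full Δ₂ is returned. That follows from the algebra for complete pairs and is not separate evidence.

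**3. Hand walk through Table 1.** Infusion time is not given. Assuming 4 h, one step is 200 + 4 × 200 = 1000 units. Suppose that AD needs the run-in dose and CD needs one step less. Doses relative to run-in are:

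| Session | 1 | 2 | 3 | 4 | 5 | 6 |
|---|---|---|---|---|---|---|
| AD | 0 | −1000 | 0 | 0 | 0 | 0 |
| CD | 0 | −1000 | −2000 | −1000 | −1000 | −1000 |

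The week-1 means are −333 (AD) and −1000 (CD), so Δ₁ = −667. The final difference is Δ₂ = −1000. The model would report:

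| Slope b | −1000 + b × 667 |
|---|---|
| 0.3 | −800 |
| 0.5 | −667 |
| 0.7 | −533 |
| 1.0 | −333 |

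With 3 h of infusion the step is 800 units, Δ₁ = −533, Δ₂ = −800, and the estimate at slope 1 is −267.

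The two-of-three rule adds instability. In this walk, sessions 1 and 2 give Δ₁ = 0 and an estimate of −1000. Sessions 1 and 3, or 2 and 3, give Δ₁ = −1000 and, at slope 1, an estimate of 0.

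**4. Simulation with the stated model.** Assumptions: 2,500 patients per scenario; run-in dose mean 3000, SD 900; CD clotting threshold 1000 units lower; threshold SD 200 to 500 units; score noise 0.1 to 0.5 of a step; no minimum-dose rule; all three sessions of each week used.

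| Infusion | Threshold SD | Δ₁ | Run-in covariate | Week-1 covariate (slope) | Share kept |
|---|---|---|---|---|---|
| 3 h | 200 | −540 | −986 | −445 (1.00) | 45% |
| 3 h | 300 | −558 | −1102 | −538 (1.01) | 49% |
| 3 h | 500 | −506 | −1058 | −524 (1.05) | 50% |
| 4 h | 200 | −658 | −998 | −337 (1.00) | 34% |
| 4 h | 300 | −637 | −1051 | −396 (1.03) | 38% |
| 4 h | 500 | −610 | −1103 | −457 (1.06) | 41% |

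With no true effect, both models gave values within 7 units of zero.

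**5. Other assumption sets.**

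- Adding Table 1's minimum-dose discontinuation rule: 32–44% kept.
- CD requirement 30% lower, 4 h infusion, AD threshold 30–90% of usual dose, score noise 150–400 units: true difference about −550 to −975, estimated as −183 to −673, so 33–69% kept. Over requirements lowered by 15–50%: 23–79%.
- CD requirement 30% lower, 3–4 h infusion, mean CHD 3000–5000: about 59–84% kept.
- CD requirement 30% lower, slope estimated within patients: 16–74% kept.

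**6. What this does to power.** With 14 completers, SD 900 and ρ = 0, the standard error is 900 × √(2/14) = 340. By normal approximation, with residual variance held fixed, power is 84% for 1000 units, 50% for 667, 35% for 533 and 16% for 333. This is illustrative, since the covariate also changes the residual variance.

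**The case against.** The strongest reply is that three sections (Study protocol, Study endpoints, Cumulative heparin dose) point to a pre-randomisation baseline and only a parenthesis in Statistical analysis departs from it. The article is condensed, so that parenthesis may be loose wording, and if the Cumulative heparin dose definition governs, no week-1 dose enters the primary estimate. This is fair as far as it goes: the bias arises if the model is run as written. But nothing limits the covariate to session 1 or to the run-in. Reading each period to include the run-in does not help either, because its first week does not contain its last session.

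Second, the covariate is only partly contaminated. Session 1 is a true baseline value, and most of the contamination sits in session 3: with sessions 1 and 2 only, one simulation lost at most about 8%. That stands, but the plan does not restrict the covariate to those sessions.

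Third, the magnitude is not stable. Infusion time, thresholds and score noise are all assumed. One set, at higher doses and a 50% effect, lost as little as 3%. Another, with the discontinuation rule, 30–50% lower CD thresholds and little score noise, gave slopes of about 1.2–1.8 and an adjusted estimate of the opposite sign. The shares are illustrations, and attenuation is the usual result, not a guaranteed one. None of this makes the week-1 dose a valid baseline.

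**Conclusion.** The concern holds: the covariate rule is wrong as written. It contradicts the article's own definition of baseline and conditions the primary comparison on post-randomisation doses that lead to the outcome. The expected consequence is an estimate pulled towards no difference, with no false effect when the dialysates are equivalent. For a 30% or 1000-unit effect, most assumption sets kept between about 16% and 84% of the true difference. The exact share cannot be fixed from the article. The conclusion itself rests only on the stated start dose, the session-by-session titration and the stated covariate. The sample size is not shown to be wrong by this point.

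**What to change.** In the Statistical analysis section, replace the week-1 covariate with the CHD of the last run-in session, one value per patient, and state that no post-randomisation dose enters the primary model as a covariate. Dropping the covariate would leave the treatment contrast unchanged for complete pairs. Keeping the run-in value is preferable, because 30% dropout is planned, incomplete pairs bring in between-patient information, and the percent-change outcome needs that baseline anyway.

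In the same edit, reconcile the outcome window: the Cumulative heparin dose section averages the last two sessions of each phase, while Statistical analysis accepts two of three second-week values.

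The cost is a sentence or two of analysis wording, best settled before unblinding. The run-in CHD is already collected, and no procedure or heparin rule changes.
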